#### Sample Size

The main aim of the study is to assess the feasibility of the design and intervention. The sample required for this is not based on a formal power calculation but on a pragmatic decision balancing sufficient numbers to be able to identify likely barriers to carrying out a larger scale trial, and cost. We aim to recruit 100 participants which will also allow us to estimate the likely effect size of the intervention on a range of outcome measures.

### Outcome measures

Relatives will be assessed on a range of measures at both baseline and follow-up. All measures are conducted in a face-to-face interview.

1) The General Health Questionnaire (GHQ-28) [12] is a 28-item version of General Health Questionnaire derived by factor analysis from the full 60-item version. It is used to assess the psychological aspect of quality of life or in the detection of psychiatric distress. Participants indicate whether their current state differs from their usual state, thereby assessing recent changes in state as opposed to long-term traits or illnesses.

2) The Family Questionnaire [13] presents participants with a range of symptoms of mental illness that have the potential to pose a problem in family life. It assesses the extent to which each of these symptoms cause the relative concern and how well the relative is able to cope with their concerns.

3) The Relationship Quality Scale [14] asks service users and relatives to rate their perception of their relationship with one another on scales of supportiveness and criticism. This measure has been shown to predict outcome for people with severe depression [14] and schizophrenia [15].

4) The Brief Illness Perception Questionnaire [16] adapted from the original Illness Perception Questionnaire [17] measures the insight of participants into their relative's illness. Components include the participant's views on the consequences of the illness, comprehension of the illness, knowledge of prognosis, the extent to which they attribute blame, knowledge of potential causes and their own concern and emotional responses to the illness.

5) The Herth Hope Index [18] consists of 12 items designed to assess hope in adults in clinical settings.

6) The Experience of Caregiving Inventory [19] measures the experience of caring for a relative with a serious mental illness. The 66-items are divided into 10 sub-scales, 8 negative (difficult behaviours, negative symptoms, stigma, problems with services, effects on the family, the need to provide back-up, dependency, loss) and 2 positive (rewarding personal experiences, good aspects of the relationship with the patient).

7) The Carer Well-Being and Support Questionnaire [20] measures the experience of carers of people with severe mental health problems. It is designed to cover all aspects of the carer's experience including relationships, roles, financial concerns, physical/emotional health, stigma, worries about safety, their satisfaction with support offered and ease of obtaining information.

8) The Relatives' Satisfaction Questionnaire (adapted from CSQ-8 [21]) is used to assess satisfaction with services in both arms of the trial to test the hypothesis that the intervention will lead to an increased level of satisfaction in relatives.

9) The Treatment As Usual Checklist is a short questionnaire designed for this study to assess the amount and type of support that participants have received from the Early Intervention Service while in the Treatment as Usual arm of the trial.

### The Intervention

#### Development

During the first year of the study a CBT oriented, supported self-management package for relatives of people with a recent onset psychosis was developed and finalised. First, a systematic review of studies of psychological interventions for relatives of people with recent onset psychosis was conducted. This identified the key components of effective interventions and distinguished them from those of ineffective interventions. Second, relatives of people who have experienced psychosis were invited to take part in focus groups to allow in-depth analysis of relatives' views and experiences of a self-management approach. The questions asked, focussed around (i) their experiences of self-management approaches; (ii) preferred format (or "health technology"); (iii) what support they would like to receive; (iv) perceived barriers. Further details on the findings of this study are reported elsewhere [22]. Finally, participants from the focus groups were invited to be part of an Intervention Reference Group that was involved in an iterative process of feedback and development to produce the supported self-management package. An independent design company was used to style the package professionally and an independent publisher was used to produce the required number of intervention packs (Figure 2).

**Figure 2 F2:**
[figure not shown]
**Development of the REACT Intervention**.

#### Features

The finalised package is modular in design, providing a range of sections or "tools" that relatives can draw on as needed. These modules have been designed to operate independently of each other and contain topics such as essential information about psychosis, ways to identify and challenge beliefs that may cause distress, ways to manage common difficulties faced by relatives, and coping strategies to aid recovery for both the relative and the person with psychosis. The package is also well referenced to guide people to existing support in related domains such as legal advice, advocacy, charities etc. Building on previous research in self-management for depression, the intervention also gives relatives the opportunity to incorporate their personal experience into the process, to situate this intervention within a context of previous experiences, build on existing self-management strategies to facilitate engagement, and highlight the self as the key agent of change [23].

The intervention has been designed to be used by relatives in their own homes and at their own convenience. As such, it has been produced as a hard copy format and as a website and participants are able to choose to use either or both of these formats. Both versions contain the same information and resources. Support is provided by an NHS support worker trained and supervised by the research team. The support worker will offer an initial face-to-face introductory session in which they guide the relative through the materials and how to use them. Following this, support in using the package will be offered via email or telephone depending on the relatives' preference.

### Analysis

#### Quantitative data

Analysis of outcomes will be carried out using simple descriptive statistics, tabulation and simple graphical display. Tests of statistical significance will be carried out using Student's t-test (quantitative outcomes) or Pearson chi-square (binary outcomes). Further analyses to allow for pre-randomisation (baseline) measures and to investigate the effects of missing outcomes will be carried out using analyses of covariance or logistic regression, respectively.

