### Design

#### Randomisation, Treatment Allocation and Blinding

This is a stratified randomised controlled trial in which participants are allocated to receive either Treatment As Usual (TAU) or TAU plus the REACT intervention. Randomisation is done using permuted blocks within Trust with block sizes varying randomly, and is carried out by an independent Clinical Trials Unit at The Christie NHS Foundation Trust, Manchester. Assessments are carried out in face-to-face interviews at baseline and at 6 months follow-up. Participants are referred into the study by Care Coordinators or self-referral. Potential participants are contacted by a research assistant (RA1) who presents them with verbal and written information about the study. If they wish to take part, the participant is asked to give written consent. Following this, a baseline interview is conducted to assess eligibility and to complete all the measures. A second research assistant (RA2) then contacts the Clinical Trials Unit and provides information about which Trust the relative is in. They are given the trial allocation by telephone. RA2 contacts the relative by telephone and post to inform them which arm of the trial they have been allocated to. RA2 contacts the relevant support worker who will guide the relative through the intervention and instructs them to arrange the first appointment with the participant. RA2 also arranges the 6 month follow-up interview date. In order to ensure that outcomes are collected blind to the treatment allocation, a letter is sent prior to this interview reminding the participant about the importance of not letting RA1 know which group they were allocated to, and making sure that the REACT toolkit is not visible in the house. This is followed-up with a phone call the day before the interview to check the appointment time is convenient and to reiterate the need to maintain blindness. RA1 conducts all of the follow-up interviews and remains blind to allocation throughout the study. To ensure blindness, all communication between relatives and NHS staff is via RA2. The RAs are housed in separate offices and receive individual supervision. Any instances of unblinding will be recorded (Figure 1).

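### The unadjusted t-test is the stated significance test, baseline-adjusted ANCOVA comes only as a further analysis, and neither is named as the source of the effect size

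*Protocol article*

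**What the plan says.** The Quantitative data section of the protocol article first promises descriptive statistics, tables and graphs. It then fixes the between-arm tests: "Tests of statistical significance will be carried out using Student's t-test (quantitative outcomes) or Pearson chi-square (binary outcomes". Baseline scores enter only in the next sentence: "Further analyses to allow for pre-randomisation (baseline) measures and to investigate the effects of missing outcomes will be carried out using analyses of covariance", with logistic regression named as the alternative. The section calls no analysis primary and names no estimator for the effect size.

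Three other parts of the article bear on this:

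- **Baseline data.** Under Outcome measures, "Relatives will be assessed on a range of measures at both baseline and follow-up". The Randomisation, Treatment Allocation and Blinding section places the baseline interview before the allocation is obtained.
- **Purpose of the estimate.** Aim (v), at the end of the Background, is to estimate the likely effect size for relatives. Under Sample Size, "We aim to recruit 100 participants which will also allow us to estimate the likely effect size of the intervention". The Discussion says that the estimates can inform later power calculations.
- **Stratification.** "Randomisation is done using permuted blocks within Trust with block sizes varying randomly". The analysis text does not mention Trust.

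**The concern.** The trial will hold a pre-randomisation score on nearly every questionnaire, yet the stated significance test makes no use of it. For a continuous outcome the baseline score is usually the strongest available predictor of the follow-up score. Leaving it out gives a wider confidence interval. It also means that a chance difference between the arms at baseline passes in part into the estimated effect.

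The sample size is fixed on pragmatic grounds, so the choice of analysis is one of the few free ways to sharpen the effect estimate. With two results per outcome and none named as the effect size, it is also open which of them will feed the planning of a later trial. What is at stake is the precision and the clear definition of that estimate, not the validity of the trial.

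**Working it through.** **Plan's own figure.** There is none to reproduce. The article says "The sample required for this is not based on a formal power calculation" and gives no alpha, power, effect size, SD or dropout rate.

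**Inputs**

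- Total sample 100 (Sample Size).
- Allocation 1:1, so n = 50 per arm. The ratio is not stated; this is an assumption.
- Outcome SD set to 1, so differences are in SD units.
- Correlation ρ between baseline and 6-month score. It is not in the article; 0.3, 0.5 and 0.7 are assumed as a range.

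**Precision**

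Unadjusted: SE = √(2/n) = √(2/50) = 0.200.

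ANCOVA on the baseline score: SE = √(2/n) × √(1 − ρ²). The variance falls by ρ². The unadjusted trial of equal precision has 100/(1 − ρ²) participants.

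| ρ | √(1 − ρ²) | SE | Variance cut | Equivalent unadjusted total | 95% CI half-width |
|---|---|---|---|---|---|
| unadjusted | 1 | 0.200 | – | 100 | 0.40 |
| 0.3 | 0.954 | 0.191 | 9% | 110 | 0.38 |
| 0.5 | 0.866 | 0.173 | 25% | 133 | 0.34 |
| 0.7 | 0.714 | 0.143 | 49% | 196 | 0.28 |

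The half-widths use t quantiles on 98 degrees of freedom (unadjusted) or 97 (ANCOVA). If only 40 per arm are analysed (20% loss, assumed), the half-width is 0.445 unadjusted against 0.425, 0.386 and 0.318. The relative gain is the same. Any further effect of adjusting for Trust is not included.

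**Chance imbalance**

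The baseline difference between arms on a given measure also has SE 0.200. The chance that it exceeds 0.3 SD in either direction is 2 × (1 − Φ(0.3/0.200)) = 2 × (1 − Φ(1.5)) = 0.134.

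Given a baseline difference b, the unadjusted 6-month difference is shifted by ρ × b. For b = 0.3 this is 0.09, 0.15 or 0.21 SD at ρ = 0.3, 0.5 or 0.7. Conditional on that imbalance, the t-test's type I error is 6.2%, 8.2% or 10.1%. Averaged over all randomisations it remains 5%.

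**If the t-test were on change scores**

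The article does not say which score the t-test uses. Since allowance for baseline is placed in the further analyses, 6-month scores are the natural reading. On change scores, with equal SDs at both visits, SE = 0.200 × √(2(1 − ρ)). That is 0.200 × √1.4 = 0.237, 0.200 × √1 = 0.200 and 0.200 × √0.6 = 0.155. ANCOVA is more precise at each assumed ρ.

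**The case against.** The strongest reply is that ANCOVA is already in the plan. A reader might infer that precision and protection from imbalance are lost altogether. They are not: the adjusted analysis will be done, and the question is only which result leads. Nor does the article call the t-test its main analysis. That is an inference from the order of the sentences and from the adjusted models being described as further analyses.

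Other limits also stand:

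- **Validity.** A reader might infer an inflated false-positive rate. The overall type I error of the t-test is 5%; only the error conditional on an observed imbalance departs from it.
- **Size of gain.** It depends on a correlation that the article does not give. At 0.3 it is small.
- **Scope.** It would be too broad to say that every outcome has a baseline value. The Treatment As Usual Checklist records support received during the trial, and recruitment, retention and attendance have no baseline score.
- **Binary outcomes.** Logistic adjustment does not shrink the standard error of the log odds ratio in the way shown above, so these figures say nothing about the chi-square test.
- **Stakes.** This is a feasibility trial, not a definitive one, and estimating the effect is one of seven aims. Gains in power for a chosen effect would measure it against a target it does not set.

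It can also be said that a short article leaves the ranking of analyses to a fuller document. That answers less, because the article does state the tests and their order. The challenge is to that stated choice, not to an omission.

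**Conclusion.** The point holds for quantitative outcomes that have a baseline score. The stated test ignores information collected before allocation, and the article does not say whether the t-test or the ANCOVA gives the effect size for aim (v).

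Under 1:1 allocation with 50 per arm analysed, the cost of taking the unadjusted result is 9%, 25% or 49% of the variance at assumed correlations of 0.3, 0.5 or 0.7. The estimate is also exposed to a shift of 0.09 to 0.21 SD when a measure is out of balance by 0.3 SD; an imbalance larger than that has about a 13% chance per measure. Effect estimation is a stated purpose and the remedy is free, so the change should be made. The documents do not support calling the planned test invalid or saying that baseline adjustment is absent.

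**What to change.** For each quantitative outcome with a baseline score, state that the lead test and effect estimate come from the ANCOVA already planned: 6-month score on arm and that measure's baseline score, with Trust as a covariate because it is the randomisation stratum. Report the adjusted difference with its 95% confidence interval and identify it as the effect size for aim (v). Keep the t-test as a descriptive supplement. For measures without a baseline value, say so and leave the unadjusted comparison in place.

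The cost is a change of wording in the analysis section. The baseline scores and Trust are already recorded, and the sample size, visits and questionnaires are unaffected.

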## Abstract

**Background:**

Mental health problems commonly begin in adolescence when the majority of people are living with family. This can be a frightening time for relatives who often have little knowledge of what is happening or how to manage it. The UK National Health Service has a commitment to support relatives in order to reduce their distress, but research studies have shown that this can lead to a better outcome for service users as well. Unfortunately, many relatives do not get the kind of support they need. We aim to evaluate the feasibility, acceptability and effectiveness of providing and supporting a Relatives' Education and Coping Toolkit (REACT) for relatives of people with recent onset psychosis.

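### Unadjusted significance tests lead the between-arm analysis of an unpowered feasibility trial whose stated aim is effect-size estimation

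*Protocol article*

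**What the plan says.** The Quantitative data section under Analysis has three steps.

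1. Description: "Analysis of outcomes will be carried out using simple descriptive statistics, tabulation and simple graphical display".
2. Inference: "Tests of statistical significance will be carried out using" the t-test for quantitative outcomes and the chi-square test for binary ones. No outcome is singled out or excluded, and the tests carry no exploratory label.
3. Further analyses by analysis of covariance or logistic regression, to take account of baseline values and to look at missing outcomes.

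Elsewhere the article sets the purpose. The last paragraph of the Background says the trial is not meant to be definitive, and aim (v) there is to estimate how large the effect on relatives' outcomes may be. Of the target of 100, the Sample Size section says: "The sample required for this is not based on a formal power calculation but on a pragmatic decision". The Discussion intends the effect-size estimates for sizing later trials.

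The Outcome measures section lists nine instruments: eight outcome scales and a checklist of usual care received. None is named as primary. For the satisfaction scale (item 8) the stated purpose is "to test the hypothesis that the intervention will lead to an increased level of satisfaction in relatives". The Abstract describes the overall aim as to "evaluate the feasibility, acceptability and effectiveness" of the toolkit.

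**The concern.** The declared purpose is feasibility and estimation, but the lead between-arm inference is a significance test without baseline adjustment. A p-value does not give the size of an effect or its precision, which is what aim (v) asks for. With several scales, no lead outcome and no power calculation, the tests can mislead in two ways: an isolated significant scale may be a chance result, and a non-significant scale may be read as showing no effect when the trial could not have detected a small to moderate one. At stake is the trial's use for planning. A later team needs a difference with an interval for each measure, not a list of scales that did or did not pass 5%.

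**Working it through.** **Inputs.** From the protocol: two arms, 100 participants (Sample Size), eight outcome scales (Outcome measures, items 1 to 8). Not stated, so assumed: 1:1 allocation (50 per arm), two-sided 5% level, true effects of 0.2 to 0.8 SD, loss to follow-up of 0 to 30% (50 down to 35 per arm). The protocol does not derive the 100 from any power calculation, so there is no stated figure to reproduce.

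**Chance of at least one false positive if there is no effect on any scale.** If the eight tests were independent: 1 − 0.95^8 = 1 − 0.663 = 0.337, about 34%. The scales are answered by the same relative, so correlation is to be expected. Simulating equally correlated normal test statistics (200,000 draws) gives 30% at correlation 0.3, 25% at 0.5 and 19% at 0.7. The expected number of false positives is 8 × 0.05 = 0.4.

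**Power of one unadjusted test.** Normal approximation: power = Φ(d√(n/2) − 1.96), with n per arm and d in SD units. At n = 50, √(n/2) = 5, so d = 0.2 gives Φ(1.0 − 1.96) = 0.169, and d = 0.4 gives Φ(2.0 − 1.96) = 0.516.

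| n per arm | 0.2 SD | 0.3 SD | 0.4 SD | 0.5 SD | 0.8 SD |
|---|---|---|---|---|---|
| 50 | 17% | 32% | 52% | 70% | 98% |
| 40 | 14% | 27% | 43% | 61% | 95% |
| 35 | 13% | 24% | 39% | 55% | 92% |

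A noncentral t calculation agrees to within about one percentage point. The effect detectable with 80% power is 0.56 SD at 50 per arm and 0.67 SD at 35.

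**What estimation would give.** The 95% half-width for an unadjusted difference is 1.96√(2/n): 0.39 SD at 50 per arm, 0.44 at 40 and 0.47 at 35. As an illustration at 50 per arm, an observed difference of 0.20 SD has an interval of 0.20 ± 0.39, that is −0.19 to 0.59. The test reports only that this is not significant. The interval shows that 0.5 SD remains compatible with the data and that 0.8 SD does not. Adjustment for baseline narrows the interval by a factor of about √(1 − r²), where r is the correlation between baseline and follow-up; the protocol gives no value for r.

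**The case against.** The strongest reply is that the article is open about its limits and already contains most of the remedy. It disclaims definitive status, says that no power calculation was made, starts with description, and plans baseline-adjusted models that yield the estimates aim (v) needs. Choice of sub-scales, handling of multiplicity and interval reporting commonly sit in an analysis plan. All of this stands, so no absence of that kind is counted here. What remains is on the page: the unadjusted tests come first, without restriction or label, and adjustment is secondary.

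Several stronger readings are tempting, but the document does not support them.

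- **That false positives are likely.** Over eight scales the chance is 19% to 34%: well above 5%, but below one half. It passes one half only if tests multiply. Item 6 says of its instrument: "The 66-items are divided into 10 sub-scales, 8 negative". Counting 7 other scales + 10 sub-scales = 17 tests gives 1 − 0.95^17 = 58% if independent, but 49%, 39% and 27% at correlations 0.3, 0.5 and 0.7. Nothing says that the sub-scales will be tested one by one.
- **That non-significant results are uninformative.** They are weakly informative about small to moderate effects, but power at 0.8 SD is 92% to 98%, so they do count against large effects.
- **That every outcome will be tested.** This is the natural reading of a sentence with no limit, but the words are not there.
- **That measures will be carried forward because they were significant, with exaggerated effects.** No progression rule or choice of outcome is tied to a p-value.
- **That a primary outcome had to be fixed now.** Aim (i) includes the acceptability of the outcome measures, so this trial may properly inform that choice.

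**Conclusion.** The concern holds as a mismatch between purpose and lead analysis. A non-definitive trial without a power calculation or a lead outcome, which aims to estimate effect sizes, puts unadjusted significance tests first and the more suitable adjusted analyses second. Its size is moderate: a 19% to 34% chance of at least one false positive over eight scales, and 17% to 52% power for 0.2 to 0.4 SD at 50 per arm, lower with losses. The figures rest on 1:1 allocation, a two-sided 5% level, one test per scale and, for the lower false-positive figures, equal correlation of up to 0.7. The power figures are for the unadjusted test; baseline adjustment would raise them somewhat. The point concerns the order and labelling of the analyses. It does not fault the sample size, which is reasonable for the feasibility aims. The word effectiveness in the Abstract is an editorial matter, since the listed aims already speak of estimation, and the finding does not depend on it.

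**What to change.** In the Quantitative data section:

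- Make the baseline-adjusted between-arm estimates (analysis of covariance or logistic regression, both already planned) with 95% confidence intervals the main output for all measures.
- Move the t-tests and chi-square tests below them, or drop them. Label any that remain as exploratory, including the test of the satisfaction hypothesis in Outcome measures item 8.
- State that no conclusion on effectiveness will be drawn from the tests.

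Naming a candidate primary outcome for the next trial is optional; the document gives no basis for preferring one scale.

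The cost is a few sentences, with no new data and no new analysis method. The downside is that there will be no p-value to headline. Keeping the tests as confirmatory with a Bonferroni correction would be a poor alternative: at 0.05/8 = 0.00625, power for 0.5 SD at 50 per arm falls from about 70% to about 41%.
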